#### Outcomes {12}

The primary endpoint is the mean difference in PaCO_2_ from baseline to 24 h after randomization. Secondary endpoints include the following: (1) the mean difference in PaCO_2_ from baseline to 6, 12, and 18 h after randomization; (2) dyspnea score at 6, 12, 18, and 24 h; (3) overall discomfort score related to the ventilatory strategy and proportion of patients showing poor tolerance to treatment at 24 h (e.g., complaining about noise, pressure, temperature, gastric distension, vomiting, or claustrophobia); (4) the proportion of patients who change treatment strategies (switch to the other ventilatory strategy or to no support); (5) rate of treatment failure, defined as the proportion of patients who had PaCO_2_ worsening or reduction < 10 mmHg from baseline, or worsening with no improvement of the dyspnea or respiratory rate > 30 breaths per minute; (6) respiratory rate; (7) rate of endotracheal intubation within 24 h; (8) length of hospital stay; and (9) all-cause mortality.

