#### Sample size calculation {14}

Based on previous studies [21], we set the non-inferiority cutoff at 5 mmHg. So, we assume that in the intervention group, PaCO_2_ may not elevate more than 5 mmHg after 24 h of the high-flow nasal cannula therapy with sequential noninvasive ventilation. According to previous studies, we also assume that the PaCO_2_ of intervention group is around 54 mmHg, and the control group is around 55 mmHg. Standard deviation is 9 mmHg, after 1:1 ratio randomization, and to assess non-inferiority using an *α* = 0.05, power = 0.80, and 1-side testing, 58 subjects were needed totally. Allowing for 10% loss to follow-up, we assume that we will need to recruit 70 patients. However, if loss to follow-up is greater than 10%, we aim to continue recruitment until 58 patients have a primary outcome recorded.

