### Statistical analysis {20}

The primary and secondary endpoints will be analyzed according to the intention-to-treat principle. We will use descriptive statistical methods to measure patient characteristics and baseline clinical features. For primary and secondary outcomes, continuous variables will be presented as means ± standard deviations or median interquartile ranges (IQR). Categorical variables will be expressed as counts with percentages. We will use Student’s *T* tests or Mann–Whitney *U* tests to evaluate the differences between treatments in continuous variables according to normal distribution. Categorical variables will be compared using chi-squared or Fisher’s exact tests. All data collected will be analyzed by an independent statistical expert using SPSS (SPSS 22.0). A *p*-value < 0.05 will be considered statistically significant.

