Above all, no matter the clinical parameters or prognosis, HFNC may be noninferior to NIV. HFNC shows advantages in better patient comfort and tolerance, fewer complications, improved warming and humidification of their respiratory tracts, and better sputum excretion. However, if AECOPD patients are asleep, HFNC may increase the risk of CO_2_ retention and respiratory acidosis. On the other hand, NIV may face failure because of discomfort related to the ventilation and the mask, decreased secretion clearance, and patient–ventilator interaction mismatch.

This study aims to try to take advantage of both the strengths of HFNC and NIV to improve clinical care for AECOPD patients in the ED and critical care environments. We believe that the work of this trial will help us better understand whether HFNC with sequential NIV has any advantages over NIV alone. If this ventilatory strategy proves beneficial or non-inferior, it could provide crucial clinical evidence for improving care for AECOPD patients.

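### The primary analysis can switch from a comparison of means to a Mann-Whitney test on the observed distribution, so what is estimated against the 5 mmHg margin depends on the data

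*Protocol article*

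**What the plan says.** Three places in the protocol article bear on this.

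- **Outcomes {12}** puts the endpoint on the scale of a mean: "The primary endpoint is the mean difference in PaCO_2_ from baseline to 24 h after randomization".
- **Sample size calculation {14}** puts the margin on the same scale: "we set the non-inferiority cutoff at 5 mmHg". It assumes that PaCO2 in the "intervention group is around 54 mmHg, and the control group is around 55 mmHg", and continues "Standard deviation is 9 mmHg, after 1:1 ratio randomization". With alpha = "0.05, power = 0.80, and 1-side testing", it concludes that "58 subjects were needed totally".
- **Statistical analysis {20}** opens by covering primary and secondary endpoints together. It allows either means with standard deviations or medians with interquartile ranges, and chooses between Student's t and Mann-Whitney U to evaluate "differences between treatments in continuous variables according to normal distribution". It names no normality criterion, makes no exception for the primary endpoint, and plans no shift estimate or interval for the Mann-Whitney branch.

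**The concern.** The endpoint, the margin and the sample size all refer to one quantity, the difference between arms in mean PaCO2 in mmHg. The analysis rule can replace that quantity once the data are in. Mann-Whitney compares rank order. As planned it returns a p-value for equality of the distributions, with no mean difference and nothing in mmHg to set beside 5.

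The two branches give nearly the same answer when the data are close to normal. They part when one arm contains a minority of patients with much higher PaCO2 than the rest, because the mean counts how high those values are and the ranks largely do not. Such a minority is also what makes a normality check fail and sends the analysis to the rank test. At stake is whether the trial reports the primary quantity it was designed for, and whether its error rate at the margin is the one intended.

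**Working it through.** **1. Reproduce the plan's sample size.** Inputs from {14}: margin 5, assumed difference 54 − 55 = −1, SD 9, one-sided alpha 0.05, power 0.80, ratio 1:1.

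Normal approximation: n per arm = 2 × 9² × (1.645 + 0.842)² / (5 + 1)² = 162 × 6.185 / 36 = 27.8, so 28 per arm and 56 in total. With the noncentral t distribution, 28 per arm gives power 0.793 and 29 per arm gives 0.806, so 58 in total. The stated 58 is the size for a t-based comparison of means.

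**2. A fixed example of the two branches.** Take 29 values per arm at evenly spaced normal quantiles, SD 9, with the intervention arm 1 mmHg lower. Then add a constant to the three highest intervention values. The mean rises by 3 × addition / 29; for +20 that is 2.07.

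| Added to 3 patients (mmHg) | Mean difference | t-based one-sided 95% upper limit | Mann-Whitney U (two-sided p) | Hodges-Lehmann shift | Its upper limit |
|---|---|---|---|---|---|
| 0 | −1.0 | 2.9 | 390 (0.64) | −1.0 | 3.1 |
| 20 | 1.1 | 6.1 | 396 (0.71) | −1.0 | 3.7 |
| 40 | 3.1 | 9.7 | 396 (0.71) | −1.0 | 3.7 |
| 60 | 5.2 | 13.4 | 396 (0.71) | −1.0 | 3.7 |

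The rank result is the same for +20, +40 and +60. Shapiro-Wilk on the intervention arm gives p = 0.0017 at +20 and less beyond, so a normality check would choose the rank branch in all three cases.

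**3. Error rate at the margin.** Assumptions that are not in the protocol:
- The trigger is Shapiro-Wilk p < 0.05 in either arm.
- The rank branch is granted a Hodges-Lehmann one-sided 95% bound compared with 5 mmHg.
- A fraction f of one arm has PaCO2 higher by R.
- The SD of 9 applies to the analysed variable.

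The true mean deficit is 5 mmHg, with 29 per arm.

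First let the tail add to the spread. With SD 9 within each component, the arm's overall SD is √(81 + f(1 − f)R²):
- f = 20%, R = 25: √(81 + 100) = 13.5
- f = 15%, R = 33.3: √(81 + 141) = 14.9
- f = 25%, R = 20: √(81 + 75) = 12.5

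Tail in the intervention arm (6,000 simulated trials each):

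| Tail | Rank branch entered | Mean Hodges-Lehmann shift (true mean 5) | False non-inferiority, switching rule | Mean-based bound |
|---|---|---|---|---|
| 20% at +25 | 32.3% | 3.70 | 9.3% | 5.8% |
| 15% at +33.3 | 69.8% | 2.88 | 16.5% | 5.9% |
| 25% at +20 | 16.7% | 4.27 | 6.7% | 5.4% |

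An independent repeat gave 9.1%, 16.0% and 6.3% for the switching rule.

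With the **same tails in the control arm**, the switching rule gave 3.3%, 1.7% and 4.2% (another run: 3.4%, 1.7% and 5.2%), against 4.1%, 3.9% and 5.4% mean-based.

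With the **intervention-arm SD held at 9**, the component SD shrinks to √(81 − f(1 − f)R²). The switching rule then gave about 7–12%, against 5–6% mean-based. A separate run over 10–20% of patients at +15 to +20 gave 6.3–9.9%, against 5.2–6.1%.

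With **normal data in both arms**, the rank branch was entered in about 10% of trials. False non-inferiority was 5.2% under either rule, and power at a difference of −1 was 0.80 under either rule.

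**The case against.** **The direction.** A reader might infer that the rule favours the intervention, because the Discussion warns that "if AECOPD patients are asleep, HFNC may increase the risk of CO_2_ retention and respiratory acidosis" and such retention would form a tail in that arm. The documents do not support this. The warning is conditional on sleep, and Intervention description {11a} moves intervention patients to NIV when asleep and overnight. Criteria for discontinuing {11b} and Provisions for post-trial care {30} also provide for stopping or escalating support on deterioration, which may limit extreme values at 24 h. The same part of the Discussion names ways in which NIV may fail, so a tail in the control arm is as plausible, and there the rule is conservative. This objection stands: the bias has no fixed sign.

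**The size.** The 16% figure needs an intervention-arm SD of about 15, where {14} assumes 9. More extreme mixtures give more: 15% of patients at +40 and 10% at +60 gave 27% and 44%. They imply SDs of √(81 + 204) = 16.9 and √(81 + 324) = 20.1, further still from the protocol. These figures show what the mechanism can do and are not a forecast. That also stands.

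**The margin.** A reader might infer that 5 mmHg cannot be applied at all in the rank branch. That goes too far. Under a pure location shift, a Hodges-Lehmann bound could be set against it. The protocol does not plan one, however, and with a tail in one arm it does not estimate the mean difference. Nor does the missing margin set this branch apart: {20} states no margin or one-sided bound for the t test either, which is a separate matter.

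**Detail left to an analysis plan.** The normality criterion and the form of the interval may well be fixed in a document not shown. The point here is the rule that the article does state, which conflicts with its own endpoint and margin.

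**Marked retention would still be seen.** Outcomes {12} counts PaCO2 worsening as treatment failure. That limits the consequence but does not repair the primary test.

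**Conclusion.** The point holds as a conflict between the stated analysis rule and the stated endpoint, margin and sample size basis. Under {20} the primary estimand depends on the observed distribution. That conclusion needs no simulation.

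Its numerical effect rests on an assumed trigger and assumed tails. At a true mean deficit of 5 mmHg, false non-inferiority is about 7–12% with an intervention-arm tail and SD 9, up to about 16% if the tail raises that SD to about 15, and 5–6% for the mean-based bound. It is about 2–4% with a control-arm tail and essentially unchanged with normal data. The documents do not establish that the trial is tilted towards non-inferiority. The correction should be made before outcomes are compared by arm. Writing the 5 mmHg margin into {20} would not be enough, because the rank branch would still estimate something else.

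**What to change.** Add to Statistical analysis {20}: *The primary endpoint is analysed as the difference between arms in mean PaCO2 change from baseline to 24 h, with its confidence interval, whatever the observed distribution; a Hodges-Lehmann / Mann-Whitney analysis is a sensitivity analysis only.* The normality-based choice may stay for secondary continuous variables such as length of stay.

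The cost is one sentence. The sample size stays at 58 evaluable patients (29 per arm, power 0.806). The downside is some efficiency if PaCO2 changes are similarly skewed in both arms: with skewness 1 and a true difference of −1, simulated power was about 81% for the mean-based bound, against 85% for the Hodges-Lehmann bound.

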### Oversight and monitoring

#### Composition of the coordinating center and trial steering committee {5d}

The coordinating center is the Peking Union Medical College Hospital. The trial steering committee consists of principal investigators responsible for interventions. Other clinicians especially the residents in every ward will be responsible for follow-up, data collection for the trial.

#### Adverse event reporting and harms {22}

Adverse events reported by the participants or noticed by the clinicians or the caring nurses will be reported directly to the DSMC and recorded in the digital case report form and data management system.

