### Assignment of interventions: blinding {17}

Because of the design of this trial using HFNC or NIV, neither the investigators nor the patients can be blinded to the treatment allocation.

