### Participant retention and withdrawal

Once the participants are enrolled, the research team has the responsibility to clarify the goal and obligation to the participants in order to achieve a low rate of loss to intervention. Before the start of the intervention, investigators will take time to educate and explain the duration of the intervention and possible adverse effects to all patients and their legal representatives in details. All patients will be informed that they have the right to withdraw from the study at any time during the intervention and the Data Monitoring Committee (DMC) will discuss and analyze the reasons for dropouts with data collectors, which will be documented in a standardized form. All efforts will be made to complete the follow-up and data collection and avoid missing data. Analyses will be conducted in complete cases. We will also perform sensitivity analyses by imputing the missing data to worst cases.

The data and safety monitoring committee (DSMC) will consist of four qualified members from the Peking Union Medical College Hospital, including at least one statistician and intensive care or respiratory expert independent from the site trial staff. The DSMC is independent from the trial researchers, blinded to the assignment, and will monitor the progress of the trial and safety issues and require data for analyses.

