The recent systematic review from Pisani et al. reported that HFNC has been used successfully in AECOPD patients as an alternative to NIV due to its reduction in work of breathing and comfort [1]. Another recent ultrasound study examined diaphragm displacement and diaphragm thickening fraction in a cross-over study including 30 AECOPD patients with hypercapnic acute respiratory failure receiving NIV for more than 24 h [20]. That study found that the diaphragm thickening fraction in the HFNC group remained unchanged which implied equivalent clinical efficacy to NIV, while improving patient comfort [12]. A single-center randomized controlled cross-over study concluded that treatment with NIV led to a greater reduction in PaCO_2_ than treatment with HFNC, but the latter was superior across a range of tolerability aspects [9, 22]. In a short-term crossover clinical trial, Rezaei et al. found no difference in any parameters between AECOPD patients treated with NIV or HFNC (e.g., respiratory rate and PaCO_2_), however, HFNC appeared better in patients with AECOPD to reduce dyspnea scores and improve respiratory distress [23]. Li et al. conducted a prospective, randomized, controlled trial which enrolled 320 patients with AECOPD who were given either HFNC or conventional oxygen therapy, finding that the PaCO_2_ of the HFNC group was lower at 24 h and these patients had improved prognoses [24]. Xu-Yan Li et al. conducted a prospective randomized controlled study comparing the effectiveness of HFNC to conventional oxygen therapy in AECOPD patients, and found HFNC had improved the treatment failure [24]. However, other prospective study compared the effect of HFNC to NIV in hospitalized severe AECOPD patients and found no significant differences in 6 and 24 h ABG analyses, as well as 30-day intubation and mortality rates [25]. HFNC has been associated with fewer complications, better tolerance, and less naso-facial skin breakdown than NIV [15]. Most significantly, Cortegiani et al. performed a multicenter, non-inferiority randomized trial comparing HFNC to NIV in nine centers in Italy. The patients they randomized to the HFNC group had worsening oxygenation during the first six hours. Subsequently, 32% of these patients underwent NIV during their hospitalization, but they also had a longer length of NIV than those originally allocated to the NIV group [17]. These findings suggest that HFNC and NIV may play a complementary role in AECOPD treatment.

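### General adverse events, naso-facial skin breakdown and secretion problems have no stated scheduled assessment or endpoint in this open-label trial, so any comparison of them between arms is open to ascertainment bias

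*Protocol article*

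**What the plan says.** **General adverse events.** The section on adverse event reporting and harms {22} says: "Adverse events reported by the participants or noticed by the clinicians or the caring nurses will be reported directly to the DSMC", and that they are "recorded in the digital case report form and data management system". It describes no solicited or timed enquiry.

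**Blinding.** Section {17} says that "neither the investigators nor the patients can be blinded to the treatment allocation". The committee receiving the reports is described differently: "The DSMC is independent from the trial researchers, blinded to the assignment" (Participant retention and withdrawal).

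**Related endpoints.** Outcomes {12} includes, as secondary endpoint (3), the "overall discomfort score related to the ventilatory strategy and proportion of patients showing poor tolerance to treatment at 24 h", with examples such as patients "complaining about noise, pressure, temperature, gastric distension, vomiting, or claustrophobia". Endotracheal intubation within 24 h and all-cause mortality are endpoints (7) and (9). Neither adverse events as a class, nor skin breakdown, nor secretions appear among the nine secondary endpoints.

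**Schedule.** Table 1 marks blood gases and RASS at start, 6, 12, 18 and 24 h. It has a 'Secretions' row without a visible mark and no adverse-event row.

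**Background.** The Discussion reports that HFNC has been associated with "fewer complications, better tolerance, and less naso-facial skin breakdown than NIV" and concludes that "HFNC shows advantages in better patient comfort and tolerance, fewer complications", adding better sputum excretion. The Objectives section {7} describes the safety of HFNC in these patients as unclear.

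**The concern.** When events are recorded because someone mentions or notices them, the count depends on attention as well as on occurrence. In an open-label trial, attention can differ by arm. Staff who expect mask injury may inspect the face of a patient on continuous NIV more often than that of a patient on HFNC by day. Secretion problems in either arm may go unrecorded if nobody asks. The committee's blinding does not help, because it sees only what unblinded people pass on.

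The stake is the safety part of the trial's message. A non-inferior PaCO2 result is likely to be read together with tolerability and complications. For skin breakdown, secretions and general adverse events, a difference could be a detection difference, and an absence of events could mean that nobody looked. What is not observed during the 24 h window cannot be reliably recovered later.

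**Working it through.** **Step 1. Which events have a stated systematic route?**

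| Event or measure | Named endpoint? | Stated timing |
|---|---|---|
| PaCO2 | Yes, primary and secondary | Start, 6, 12, 18, 24 h |
| RASS (covers drowsiness) | No | Start, 6, 12, 18, 24 h |
| Discomfort score | Yes | Table 1: start and 24 h; text of {18}: the established time points |
| Poor tolerance, with vomiting, gastric distension and claustrophobia among its examples | Yes | 24 h |
| Intubation | Yes | Within 24 h |
| Death | Yes | In hospital |
| Naso-facial skin breakdown | No | None stated |
| Secretion problems | No | Table 1 row, no visible mark; nothing in {12} or {18} |
| Other adverse events | No | None stated; reported or noticed |

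The gap is the last three rows. The tolerance endpoint fills it only in part. Its examples are framed as complaints and omit skin breakdown and secretions. Data collection {18} also describes recording poor tolerance in patients who do not interrupt treatment or withdraw, so on that wording a patient whose complication led to stopping may not be counted.

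**Step 2. Is there a figure in the plan to test?** No adverse-event rate, detection rate or safety sample size is given. The only usable input is the evaluable total of 58 in the sample size section {14}, or 29 per arm. That figure reproduces. With margin 5, SD 9, true difference -1, one-sided alpha 0.05 and power 0.80, the normal formula gives 2 x 81 x (1.645 + 0.842)^2 / 6^2 = 27.8, so 28 per arm (56 in total). The noncentral t calculation gives 29 per arm (58 in total, power 0.806).

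**Step 3. What could unequal detection do? (All rates are assumptions.)** Let both arms have the same true rate t, with detection 0.9 in one arm and d in the other. The apparent difference is t x (0.9 - d).

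| t | d = 0.8 | d = 0.6 | d = 0.5 |
|---|---|---|---|
| 0.20 | 0.02 | 0.06 | 0.08 |
| 0.30 | 0.03 | 0.09 | 0.12 |
| 0.40 | 0.04 | 0.12 | 0.16 |

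In counts, for t = 0.20 and d = 0.5: 29 x 0.20 = 5.8 true events per arm; 5.8 x 0.9 = 5.2 and 5.8 x 0.5 = 2.9 recorded; ratio 0.5/0.9 = 0.56.

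**Step 4. Could the trial test such a difference formally?** Five of 29 against 3 of 29 gives a two-sided Fisher p of 0.71. For true differences, power at 29 to 35 per arm (58/2 to 70/2; two-sided alpha 0.05, normal approximation, assumed rates) is:

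| Rates | Power |
|---|---|
| 10% vs 2% | 0.25 to 0.29 |
| 20% vs 5% | 0.41 to 0.47 |
| 30% vs 10% | 0.48 to 0.55 |
| 40% vs 10% | 0.77 to 0.84 |

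Unless differences are large, safety counts here are descriptive. Their worth then depends on even collection in the two arms.

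**The case against.** The strongest reply is that this is a condensed journal article. Event definitions, grading and case report form content usually sit in documents not shown, and the harms section does not say that spontaneous reporting is the only route. This stands in part: the absence of grading or causality rules is no finding. But the article does state how events come to notice, and that statement describes unsolicited capture.

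A second reply is that much is already collected systematically. This stands. A reader might infer that all harms depend on someone volunteering them; endpoints (3), (7) and (9) show otherwise. A reader might also infer that CO2-related drowsiness on HFNC is not looked for; RASS and blood gases at every time point, with continuous monitoring, contradict that.

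Third, a complication advantage is not a hypothesis of this trial. It appears in the Discussion as background from earlier studies, and neither the objective nor the endpoints adopt it. So the documents do not support saying that the trial fails to test its own claim, or that its benefit-risk conclusion is unsound. The interest in safety expressed under Objectives still makes even recording worthwhile.

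Fourth, the unmarked 'Secretions' row may be a fault of text extraction. The timing therefore needs confirming and is not shown to be missing. Even so, neither {12} nor {18} says how or when secretions are assessed.

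Fifth, intervention patients also receive mask NIV when asleep and overnight (Intervention description {11a}). Both arms are exposed to the mask, so a detection gap as wide as 90% against 50% for the same injury may be too pessimistic. This stands and is a reason not to rely on any one cell in the working.

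**Conclusion.** The point holds in a narrow form. General adverse events are captured as participants report them or staff notice them, in an open-label setting, and skin breakdown and secretion problems have no stated scheduled assessment or endpoint. A comparison of these events between arms is open to ascertainment bias.

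No figure in the protocol is wrong because of this, and the primary PaCO2 conclusion is not affected. The size and direction of any bias cannot be derived from the document; the 2 to 16 percentage points rest wholly on assumed true and detection rates. The conclusion assumes that documents not shown contain no solicited safety form. If one exists, the remedy is to say so in the article. The change is worth making because it is cheap and must be in place before data are collected.

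**What to change.** - Keep spontaneous reporting as it is.
- Add a short fixed yes/no item set: naso-facial skin breakdown, secretion retention, vomiting or aspiration, gastric distension, device removal. The same staff complete it identically in both arms at the existing 6, 12, 18 and 24 h assessments. Drowsiness needs no new item, because RASS is already scored.
- Add an adverse-event row to Table 1 and confirm the time points for 'Secretions'.
- Add event counts by arm to Outcomes {12} as a safety outcome, reported descriptively.

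The cost is a few minutes per assessment and more minor events on record in both arms. No extra visit, assessor or procedure is needed. Assessors remain unblinded, so the bias is reduced but not removed, and the report should say so.
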